### **3. Analysis of exploratory endpoints**

3.1 The association between these 5 secondary endpoints and potential predictors (tumor size at diagnosis, tumor grade, tumor depth, tumor immune infiltration, patient age, patient sex) will be assessed by Cox proportional hazards model.

3.2 The association between germline mutations and response, toxicity and cancer outcome will be investigated using logistic regression model.

3.3 The impact of radiation on local and systemic immune responses will be evaluated using tumor and blood specimens, and these immunologic changes will be related back to patient outcomes.

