**STRATIFICATION:**

Patients will be stratified into two cohorts according to the previous administration of neoadjuvant chemotherapy.

Cohort A: neoadjuvant radiotherapy alone

Cohort B: neoadjuvant chemotherapy and radiotherapy

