#### **ELIGIBILITY CRITERIA:**

- Histologically confirmed soft tissue sarcoma of the extremity/trunk.
- Planning to undergo standard preoperative radiotherapy
- Resectable primary lesion (patients with pre-existing metastasis will be included if the primary lesion will be resected)
- Age  $\geq 12$
- KPS  $\geq 70$  or ECOG 0-2
- If a woman is of childbearing potential, a negative serum or urine pregnancy test must be documented.

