### **2. Analysis of secondary endpoints**

2.1 Interim Reports for the Primary Endpoint grade  $\geq 2$  radiation morbidity (subcutaneous tissue fibrosis, joint stiffness, or edema) at 2 years. Interim reports will be prepared yearly until the results of the study are published. In general, the interim reports will contain information about patient accrual rate with projected completion dates, status of QA review and compliance rate of treatment per protocol, and the frequencies and severity of toxicity.

2.2 Analysis of efficacy with 5 secondary endpoints (local control, regional control, distant control, progression-free survival, and overall survival)

2.2.1 Kaplan-Meier analysis will be carried out and used to estimate the local control, regional control, distant control, progression-free survival, and overall survival rates.

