### **SAMPLE SIZE JUSTIFICATION:**

The original study was designed to test for a 20% absolute improvement in the rate of grade  $\geq 2$  radiation morbidity (subcutaneous tissue fibrosis, joint stiffness, or edema at 2 years ( $\pm 3$  months) from 37% in the preoperative RT arm of the CAN-NCIC-SR2 study to 17% which requires 41 patients per cohort with 5% type I error and 80% statistical power. Allowing for 20% of patients being ineligible or not analyzable at 2 years, the total sample size needed is 51 patients. **The study met this initial endpoint(6).**

**The expansion cohort** of this study aims to evaluate non-inferiority of major wound complication rate in cohort B (neoadjuvant chemotherapy and radiotherapy) versus patients in cohort A (radiotherapy alone). One-sided two-sample proportion test will be carried out to assess the non-inferiority of major wound complication rate in cohort B compared to cohort A. According to a recent study on rates of wound complications in patients receiving preoperative RT(8), we assume the wound complication rate in cohort A to be 21% (79% success rate). We also assume that for every patient enrolled in cohort B, at least three patients will be enrolled in cohort A. With significance level 0.1 and power 80%, the enrollment of at least 41 patients in cohort B will enable us to detect a 15% increase in the wound complication rate of cohort B, which would translate to a 36%

wound complication rate (64% success rate)(9). A wound complication rate of 36% has previously been considered acceptable for patients receiving standard preoperative radiotherapy and surgery(2). We set the minimum enrollment number to 123 for cohort A and 41 for cohort B. To account for a 20% rate of potential screening failures or participant dropouts, the total enrollment goal for the expansion cohort is 205 patients.

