### **3.0 PATIENT SELECTION**

#### **3.1 Conditions for patient eligibility**

- 3.1.1 Histologically confirmed soft tissue sarcoma of the extremity/trunk
- 3.1.2 Planning to undergo standard preoperative radiotherapy
- 3.1.3 Resectable primary lesion (patients with pre-existing metastasis will be included if their primary is still going to be resected)
- 3.1.4 Age  $\geq 12$
- 3.1.5 KPS  $\geq 70$  or ECOG of 0 - 2
- 3.1.6 If a woman is of childbearing potential, a negative serum or urine pregnancy test must be documented.

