## 10.0 STATISTICAL CONSIDERATIONS

### 10.1 Statistical considerations

1. Interim Reports for the Secondary Endpoint Grade  $\geq 2$  radiation morbidity (subcutaneous tissue fibrosis, joint stiffness, or edema) at 2 years

Interim reports will be prepared yearly until the results of the study are published. In general, the interim reports will contain information about patient accrual rate with projected completion dates, status of QA review and compliance rate of treatment per protocol, and the frequencies and severity of toxicity.

2. Estimation of Secondary Endpoints Related to the safety and efficacy

Cumulative incidence approach (K-M plots and COX proportional hazard modeling) will be used to estimate the local failure, regional failure, distant metastasis, progression-free survival, and overall survival rates.

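### The exploratory Cox models for progression-free and overall survival omit metastasis at entry, although metastatic patients are eligible, so a predictor associated with metastasis can take up part of the effect of stage (minor)

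*Protocol*

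**What the plan says.** The Synopsis eligibility criteria state that "patients with pre-existing metastasis will be included if the primary lesion will be resected", and Section 3.1.3 repeats this: "patients with pre-existing metastasis will be included if their primary is still going to be resected".

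Item 2.2 of the Synopsis statistical methods defines the outcomes: "Analysis of efficacy with 5 secondary endpoints (local control, regional control, distant control, progression-free survival, and overall survival". Item 3.1, under exploratory endpoints, says that the association of these endpoints with "potential predictors (tumor size at diagnosis, tumor grade, tumor depth, tumor immune infiltration, patient age, patient sex" "will be assessed by Cox proportional hazards model". It does not say whether the models are univariable or multivariable.

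Three other places could have dealt with stage and do not:
- Synopsis, Stratification: "Patients will be stratified into two cohorts according to the previous administration of neoadjuvant chemotherapy". Metastasis is not a stratum.
- Synopsis 2.2.1: Kaplan-Meier estimates, with no split by metastasis.
- Section 10.1: "Cumulative incidence approach (K-M plots and COX proportional hazard modeling) will be used to estimate the local failure", and likewise for the other endpoints. No covariate, stratum or restriction to patients without metastasis is named.

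The study calendar (Section 8.0) schedules a chest CT and imaging of the primary site before the study.

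**The concern.** Patients who are already metastatic at entry plausibly have a different hazard of progression and death from day one. If they are over-represented among, say, large or high-grade tumours, a model that contains size or grade but not stage attributes part of that difference to size or grade. A feature with no association of its own within stage could then be reported as prognostic. This matters because finding prognostic tissue characteristics is a declared exploratory objective. The protocol also writes the predictor list out, so an analysis plan that followed it literally would carry the omission forward.

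**Working it through.** The plan states no figure on this point, so there is none to reproduce. The check has two parts.

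**1. Text.** Metastatic patients are eligible in both places where eligibility is given. The list in 3.1 has six entries and none is stage. Stratification is by chemotherapy only, and the Kaplan-Meier and Cox passages name no stage adjustment. The omission is therefore a fact of the text.

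**2. Size.** From the documents: n = 123 + 41 = 164 ("We set the minimum enrollment number to 123 for cohort A and 41 for cohort B"). Everything else is assumed: the share metastatic at entry, the association with the predictor, and the hazard ratio h for metastasis.

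*Mechanism.* Let p1 and p0 be the metastatic shares in patients with and without a binary predictor that has no effect within stage. At the start of follow-up the hazard ratio seen without stage is

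HR(0) = (1 - p1 + p1·h) / (1 - p0 + p0·h).

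With 20% metastatic overall, a 50/50 predictor and an odds ratio of 4, p0 = 0.098 and p1 = 0.302:
- h = 3: (0.698 + 0.906) / (0.902 + 0.294) = 1.604 / 1.196 = 1.34
- h = 5: (0.698 + 1.510) / (0.902 + 0.490) = 2.208 / 1.392 = 1.59

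The Cox estimate averages over follow-up, during which metastatic patients leave the risk set sooner, so it is smaller: 1.28 and 1.42 in the simulation below.

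*Simulation A (null grade effect).* Baseline hazard 0.12 per year, censoring uniform over 1-6 years, about 300 runs per setting, odds ratio 2-4, h = 3 or 5, stage omitted:

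| Metastatic at entry | Estimated HR (true 1.0) | False positives at nominal 5% |
|---|---|---|
| 5% | 1.05-1.10 | 3-7% |
| 10% | 1.07-1.22 | 7-12% |
| 20%, odds ratio 2 | 1.15-1.22 | 6-11% |
| 20%, odds ratio 4 | 1.28-1.42 | 19-29% |

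Monte Carlo error is not small. For the 19.3% entry the standard error is √(0.193 × 0.807 / 300) = 0.023, so its 95% range is about 15-24%.

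With metastasis added as a covariate, rejection was 2-7% over all settings, and the estimated HR was 0.98-1.03 where every run converged. With no association (odds ratio 1), omission gave HR 0.97-1.03, so no spurious effect.

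*Simulation B (null size effect).* Baseline hazard 0.10 per year, follow-up uniform over 1-8 years cut at 5, 600 runs per setting, metastasis three times as frequent with large tumours, h = 3-4. The HR without stage was 1.06-1.10 at 5% metastatic, 1.13-1.18 at 10%, 1.23-1.28 at 15% and 1.37-1.44 at 25%. False positives were about 5%, 7-9%, 11-17% and 25-31%. With stage in the model they were 4-7%.

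The two sets agree in direction and approximate size. Neither fits all six predictors together, and neither models immune infiltration.

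**The case against.** **The analysis is exploratory, the word used is potential predictors, and adjustment sets are often left to the analysis plan.** This stands as to severity. It does not remove the point, because the protocol did not leave the list open: it wrote one out that omits a known baseline factor which its own eligibility rules admit.

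**Metastasis at entry may be partly a consequence of size, grade or depth.** The unstratified association is then a legitimate prognostic quantity, and stratifying removes part of it. This is the strongest objection. It argues for showing both results. It does not argue for showing only the unstratified one, which cannot separate a feature that predicts outcome within stage from one that marks stage.

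**Stronger readings that the documents do not support:**
- A reader might infer that size, grade and immune infiltration *will* take up the effect of stage. That needs a material metastatic share and an association with each predictor, and the documents give neither. For infiltration even the direction is unknown.
- A reader might infer serious harm even without association, because omitting a covariate pulls Cox hazard ratios toward 1. The effect is small: a true HR of 2 becomes about 1.87-1.92.
- A reader might infer that full metastatic status is established for every patient. The scheduled imaging covers only the chest and the primary site, so metastasis elsewhere is known only if recorded at eligibility.

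**Conclusion.** The point holds as a conditional one of minor severity. The omission is certain, and its effect depends on inputs that the documents do not give. With a metastasis hazard ratio of 3-5 and a positive association with the predictor, the bias is negligible at about 5% metastatic. The spurious HR is about 1.1-1.2 at 10% and about 1.2-1.4 at 20%. False-positive rates of about 20-30% arise only at 20-25% metastatic with strong association (odds ratio near 4, or a threefold difference in frequency). The primary wound-complication comparison, the sample size and the Kaplan-Meier estimates for the whole group do not depend on these models.

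**What to change.** In item 3.1 of the Synopsis statistical methods, state that the Cox models for PFS and OS are stratified by metastasis at entry (yes/no, as recorded at eligibility and pre-study imaging), with the unstratified result shown alongside. Report the PFS and OS curves by that status. Stratification works whether the models are univariable or multivariable, and it does not assume proportional hazards between the two groups.

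The cost is a line or two of protocol or analysis-plan wording and no new procedure. There are two downsides. The stratified hazard ratio excludes any part of a predictor's association that acts through metastasis already present at entry, which is why both results should be shown. If few patients are metastatic (5% of 164 is about 8), their separate curve will be imprecise and should be read as descriptive.

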In our initial cohort, we excluded patients receiving neoadjuvant chemotherapy, which is given in patients with highest-risk disease. Currently, patients receiving neoadjuvant chemotherapy receive conventional 5-week preoperative radiation therapy, or in some cases, an abbreviated 8-day course of 28 Gy(7). Now, we propose an expansion cohort to examine our novel 5-day regimen in patients receiving either neoadjuvant RT alone or neoadjuvant RT following neoadjuvant chemotherapy. The goal of this expansion cohort is to compare toxicity outcomes in patients receiving neoadjuvant chemotherapy with patients receiving radiotherapy alone. Should the rate of toxicity be similar in each cohort, then the 5-day approach can become incorporated as a standard-of-care for all patients regardless of the use of neoadjuvant chemotherapy.

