#### **INTERVENTION AND MODE OF DELIVERY:**

Hypofractionated radiation will be delivered in the pre-operative setting to patients with soft tissue sarcoma with external beam radiation therapy. Patients in cohort A will receive 6.0 Gy x 5 fractions delivered daily in 5 fractions. Patients in cohort B will receive 5.0 Gy x 5 fractions delivered daily in 5 fractions. Patients will not be treated on weekends or holidays as is standard practice for radiation treatments.

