## 5.0 TREATMENT PLAN

### 5.1 Radiation Simulation and Planning

Each patient will undergo radiation simulation and planning. A custom vacloc bag, alpha cradle, or equivalent immobilization device will be used. A CT and/or MRI simulation will be obtained with or without IV contrast, which is standard of care for any patient undergoing radiation therapy for soft tissue sarcomas.

The study investigator will be responsible for delineating the gross tumor volume (GTV) using the CT as well as MRI imaging (if available) performed as part of staging. Guidelines for contouring will be as per the currently open NRG trial for sarcomas. In general this suggests a margin of 3 cm in the superior and inferior directions on the gross tumor volume and a 1.5 cm radial expansion. This expansion should also include any suspicious edema as seen on T2 weighted MRI. This clinical target volume (CTV) will be cropped out of natural anatomic boundaries of spread, such as bone and uninvolved muscle compartments. The CTV will then be expanded to a planning treatment volume (PTV) using a 3-5 mm expansion.

A prescription dose of 6 Gy x 5 fractions (30 Gy) will be delivered to at least 95% of the PTV. No more than 10% of the PTV should receive greater than 120% of prescription dose, and areas receiving >110% of the prescription dose should be restricted to the GTV. Intensity modulated radiation therapy (IMRT) planning techniques may be used in order to minimize radiation dose to nearby organs at risk (OAR) but is not required.

Delineation of normal structures including the bone and skin will be performed and verified by the responsible study investigator. The radiation physicist or dosimetrist will optimize the treatment plan prior to approval for treatment. Dose volume histograms (DVH) and normal tissue constraint parameters specified below will be used to judge the plan quality and optimize PTV coverage with OAR sparing prior to approval.

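### The exploratory Cox models list six predictors but not cohort, so hazard ratios for tumour predictors can be confounded with chemotherapy and radiation dose

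*Protocol*

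**What the plan says.** Under the heading "Analysis of exploratory endpoints", item 3.1 relates the five secondary time-to-event endpoints to a bracketed list that opens with tumour size, grade and depth and continues "tumor immune infiltration, patient age, patient sex) will be assessed by Cox proportional hazards model". Cohort, chemotherapy and dose are not in the list. The sentence does not say whether the models are univariable or multivariable, or whether they are pooled over cohorts, fitted within cohort or stratified. Section 10.1, item 2, names Cox modelling again without covariates or strata. Item 2.2.1 plans Kaplan-Meier estimates without saying whether they are given by cohort.

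Elsewhere the protocol describes two different groups:

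- Stratification: "Patients will be stratified into two cohorts according to the previous administration of neoadjuvant chemotherapy". This defines the cohorts; it does not say how any model is fitted. The design is non-randomized.
- Synopsis, on the initial cohort: "we excluded patients receiving neoadjuvant chemotherapy, which is given in patients with highest-risk disease".
- Intervention and Mode of Delivery: "Patients in cohort A will receive 6.0 Gy x 5 fractions delivered daily in 5 fractions", and "Patients in cohort B will receive 5.0 Gy x 5 fractions delivered daily in 5 fractions".

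Section 5.1 gives a single prescription for all patients: "A prescription dose of 6 Gy x 5 fractions (30 Gy) will be delivered to at least 95% of the PTV". This does not agree with the cohort-specific doses, and the two places must be reconciled. The present point uses the cohort-specific statement only because it is the one that mentions both cohorts.

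**The concern.** Neoadjuvant chemotherapy is described as going to the patients at highest risk, and the eligibility criteria set no limit on size, grade or depth. It is therefore plausible that large, deep or high-grade tumours are more common in cohort B. Cohort B also differs from cohort A in systemic treatment and in stated radiation dose, either of which may affect local control, metastasis or survival.

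When both links exist, cohort confounds the tumour predictors. A pooled hazard ratio for grade, for example, would mix the effect of grade with the effect of receiving the cohort B treatment. At stake is how these exploratory associations are read: a predictor may look prognostic when it is not, or a real one may look weaker. No sample size or decision rule rests on these models.

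**Working it through.** **No figure to reproduce.** The protocol gives no event count, power or expected hazard ratio (HR) for these models, so the check asks only how large the distortion could be.

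**Inputs from the protocol.** Minimum enrolment is 123 in A and 41 in B (Sample Size Justification), so the share in B is 41/164 = 0.25. The stated doses are 6.0 × 5 = 30 Gy in A and 5.0 × 5 = 25 Gy in B. With the α/β of 4 from Section 2.0 and the usual linear-quadratic expression nd(1 + d/(α/β)), the biologically effective doses are 30 × (1 + 6/4) = 75 Gy and 25 × (1 + 5/4) = 56.25 Gy. The second is 25% lower. This shows only that cohort carries a treatment difference; it says nothing about which dose is right.

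**Assumed inputs (not in the protocol).** One binary predictor G, present in 50% of A and in 50%, 70% or 90% of B. Residual cohort HR (B versus A, given G) of 0.7 to 2.0. Baseline hazard 0.12 per year, exponential times, censoring at 5 years, two-sided 5% test.

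**Hand check.** If G has no effect, the hazard ratio for G at time zero in a model without cohort is

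[1 + P(B|G=1)(HR − 1)] / [1 + P(B|G=0)(HR − 1)], where HR is the cohort HR.

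For 90% versus 50%:

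- P(G=1) = 0.25 × 0.9 + 0.75 × 0.5 = 0.60
- P(B|G=1) = 0.225/0.60 = 0.375
- P(B|G=0) = 0.025/0.40 = 0.0625

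Cohort HR 2.0 gives 1.375/1.0625 = 1.29. Cohort HR 0.7 gives 0.8875/0.98125 = 0.90.

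For 70% versus 50%, P(B|G=1) = 0.175/0.55 = 0.318 and P(B|G=0) = 0.075/0.45 = 0.167. Cohort HR 1.5 gives 1.159/1.083 = 1.07. If prevalence is equal, or the cohort HR is 1, the ratio is exactly 1.

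**Simulation.** 164 patients, 2,000 replicates per row, true HR for G = 1.0:

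| G in B / A | Cohort HR | HR, cohort omitted | False positives | HR, cohort included | False positives |
|---|---|---|---|---|---|
| 50% / 50% | 2.0 | 1.00 | 4.6% | 1.00 | 5.0% |
| 90% / 50% | 1.0 | 1.01 | 4.8% | 1.00 | 5.1% |
| 70% / 50% | 1.5 | 1.07 | 5.5% | 1.01 | 4.8% |
| 70% / 50% | 2.0 | 1.12 | 7.2% | 1.00 | 4.2% |
| 90% / 50% | 1.5 | 1.16 | 8.6% | 1.01 | 5.0% |
| 90% / 50% | 2.0 | 1.25 | 15.6% | 0.99 | 5.1% |
| 90% / 50% | 0.7 | 0.90 | 7.3% | 1.00 | 4.8% |

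The simulated values agree with the hand check. In the 90%/50%, HR 2.0 row the simulated value is nearer 1 (1.25 against 1.29), as expected when higher-risk patients leave the risk set during follow-up.

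With a true HR of 2.0, the estimate without cohort ranges from 1.80 (90%/50%, cohort HR 0.7) to 2.42 (90%/50%, cohort HR 2.0). With cohort included it is 2.00 to 2.03.

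**A more strongly confounded setting.** With 90% versus 40%, cohort HR 2, no true effect, 7-year accrual and a data cut at year 8 (600 data sets), the median HR is 1.34 with 16% false positives when cohort is omitted. Stratified by cohort, it is 1.02 with 5%.

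**Price of adjusting when it is not needed.** With a true HR of 2.0, 90%/50% and cohort HR 1.0, power is 90.2% without cohort and 86.5% with it, a loss of 3.7 points.

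**The case against.** Four objections deserve weight.

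1. *The wording does not exclude cohort.* Item 3.1 is one sentence naming predictors of interest. It does not forbid adjustment or stratification, and such detail is commonly left to the SAP, which is not available here. This stands as a limit on certainty: the protocol does not prescribe a pooled model without cohort. But the protocol itself names the variables and leaves out the treatment group, so an analyst following the list would omit it.

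2. *The bias is conditional.* A reader might infer that the tumour predictors necessarily absorb the cohort effect. The documents do not support that. They describe higher risk in chemotherapy patients but give no predictor distribution and no cohort effect. Higher baseline risk and benefit from chemotherapy may work in opposite directions. If all six predictors enter together and baseline risk differs only through them, only the chemotherapy and dose effect is left to confound. This objection stands in full.

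3. *The pooled hazard ratio answers a legitimate question.* It describes prognosis under treatment as given, and since tumour features influence who receives chemotherapy, cohort is partly a consequence of them. This stands in part. It is a reason to keep the pooled estimate as an addition, but taken alone, an estimate across two different regimens is hard to interpret.

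4. *Immune infiltration, age and sex.* The documents do not say that these differ by cohort. Item 3.1 also does not say whether infiltration is measured on the pre-treatment biopsy or the surgical specimen, so a claim that this biomarker is confounded would go too far.

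**Conclusion.** The point holds as a conditional and minor one. The listed predictors omit cohort, and the protocol's own description makes confounding of size, grade and depth plausible. Under the assumed inputs a true hazard ratio of 1.0 is estimated at 0.90 to 1.25, or 1.34 in the 90% versus 40% setting, with false-positive rates of 5% to 16%. In null or mild settings the estimate is 1.00 to 1.07. The direction cannot be predicted from the documents. All these figures rest on assumed prevalences, cohort effects and event rates; only the cohort sizes come from the protocol.

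It would also be wrong to infer that the trial's main conclusion is at risk. The comparison of major wound complications is a separate two-sample test of proportions and does not use these models.

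**What to change.** Add one sentence to item 3.1: the Cox models are stratified by cohort (A or B), or include cohort as a covariate, with the pooled unadjusted association as an optional sensitivity analysis. State in item 2.2.1 that Kaplan-Meier estimates are presented by cohort. The same sentence can be carried into Section 10.1, item 2, so that the two places agree. Separately, reconcile the dose statement in Section 5.1 with the cohort-specific doses under Intervention and Mode of Delivery.

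Cohort is known for every patient, so no data collection or sample size changes. Stratification yields no hazard ratio for cohort and gives up a little precision with about 41 patients in B. Where a cohort estimate is wanted, entering cohort as a covariate avoids the first drawback.

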### **1.3 Exploratory objectives**

Collect germ-line DNA and nucleic acids from cancer patients to further investigate the association and identify new germ-line mutations that impact cancer predisposition

Investigate the role of germ-line mutations in predicting cancer outcome, toxicity, and response to therapy

Evaluate pre-treatment, post-radiotherapy and, if applicable, metastatic or relapse tissue specimens for characteristics including DNA alterations, gene expression, protein expression, immunophenotype and Intratumoral heterogeneity that may be predictive, prognostic or explain resistance.

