#### **5.4 Patient Follow-up after Treatment**

Patients will be seen in clinic within 3 months after the completion of radiation by either the radiation oncologist or the surgeon. After this, follow-up will be performed every 6 months after the time of surgery for the first 5 years after treatment (+/- 2 months). The patients will be followed both clinically and radiographically after treatment. CT or MRI will be performed of the primary site and CT of the chest every 6 months (+/- 2 months) for the first 2 years and then once at the end of year 3, or at the investigators' discretion. Whenever feasible and in the best interest of subjects, follow-up visits may occur via telemedicine.

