### 10.2 Patient Accrual and Study Duration

#### 10.2.1

The accrual of the initial cohort of the study (N=52) was completed enrollment on 6/11/2018. It is expected that the expansion cohort of the study protocol will complete accrual within 7 years after the initiation of the expansion cohort. To account for potential screening failures or participant dropouts, the total enrollment goal for the expansion cohort is 205 patients.

The study expansion will then continue for an additional 1 year to obtain follow-up data for the primary endpoint for the expansion phase of the study.

Study-related data will be stored for 5 years after termination of the study accrual and when all patients have completed follow-up procedures.

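### Item 3.2 uses logistic regression for germline associations with cancer outcome, with no horizon or censoring rule, although the protocol treats its disease outcomes as censored times elsewhere

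*Protocol*

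**What the plan says.** The germline objective in Protocol section 1.3 is "Investigate the role of germ-line mutations in predicting cancer outcome, toxicity, and response to therapy", so cancer outcome is listed separately from toxicity and response. The synopsis, under analysis of exploratory endpoints, item 3.2, gives all three one method: "The association between germline mutations and response, toxicity and cancer outcome will be investigated using logistic regression model". No time point is named, and nothing is said about patients whose follow-up ends early.

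Elsewhere the protocol handles its disease outcomes as times to event:

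- Item 2.2.1: "Kaplan-Meier analysis will be carried out and used to estimate the local control, regional control, distant control, progression-free survival, and overall survival rates".
- Item 3.1, directly above 3.2, relates those five endpoints to tumour size, grade, depth, immune infiltration, age and sex. It ends "patient age, patient sex) will be assessed by Cox proportional hazards model". Germline status is not in the list.
- Section 10.1: "Cumulative incidence approach (K-M plots and COX proportional hazard modeling) will be used" for the same outcomes.

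On timing, section 10.2.1 expects that the expansion cohort "will complete accrual within 7 years after the initiation of the expansion cohort" and adds: "The study expansion will then continue for an additional 1 year to obtain follow-up data for the primary endpoint". Section 5.4 schedules visits every 6 months up to 5 years. No date is given for the germline analysis.

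**The concern.** Logistic regression suits response, and toxicity at a set time. For a disease outcome observed over unequal periods, a plain yes/no model counts a patient last seen event-free at 1 year the same as one seen event-free at 5 years, and it discards when events happened. Two consequences follow. The odds ratio becomes a blend over whatever follow-up was accrued, so it cannot be read as a 2-year or a 5-year effect or set beside the hazard ratios from item 3.1. A real association is also less likely to be detected. Because item 3.1 omits germline status, the Cox analyses already planned do not cover this question.

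**Working it through.** **Inputs from the protocol.** Minimum size is 123 + 41 = 164, and the enrolment goal is 164 / 0.8 = 205. Accrual lasts up to 7 years, plus 1 further year. Scheduled follow-up runs to 5 years. The protocol gives no carrier frequency, event rate, effect size or power for this analysis, so there is no planned figure to reproduce.

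**Assumptions.** 30% carriers; exponential event times; five-year event risk in non-carriers of 10, 30, 50 or 70%; hazard ratio 1 or 2; uniform accrual; data cut at year 8; follow-up unrelated to genotype; two-sided 5% test; 2,000 simulated trials per setting.

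**Step 1, follow-up at a year-8 cut.** Follow-up is min(5, 8 − entry time). Entry in the first 3 of 7 years gives the full 5 years (3/7 = 43%). The other 4/7 = 57% have between 1 and 5 years, 3 on average. Mean follow-up is 3/7 × 5 + 4/7 × 3 = 3.9 years.

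Check on the simulation, with 30% risk, hazard ratio 1 and N = 205: λ = −ln(0.7)/5 = 0.0713. The event probability over the 1-to-5-year group is 1 − (e^−λ − e^−5λ)/(4λ) = 1 − (0.931 − 0.700)/0.285 = 0.190. Overall it is 3/7 × 0.300 + 4/7 × 0.190 = 0.237, and 205 × 0.237 = 48.6 events. The simulation also gave 48.6.

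**Step 2, the odds ratio depends on the horizon.** With hazard ratio 2, carrier survival is S², where S is non-carrier survival at time t. The odds ratio is [(1 − S²)/S²] / [(1 − S)/S] = 1 + 1/S. At 30% five-year risk, the 5-year value is 1 + 1/0.7 = 2.43. At 1 year S = 0.7^(1/5) = 0.931, which gives 2.07.

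**Step 3, results at the year-8 cut, N = 164, hazard ratio 2.**

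| Five-year risk, non-carriers | True 1-year OR | True 5-year OR | Crude logistic OR | Cox power | Logistic power | Loss (points) |
|---|---|---|---|---|---|---|
| 10% | 2.02 | 2.11 | 2.05 | 27% | 27% | about 0 |
| 30% | 2.07 | 2.43 | 2.26 | 64% | 61% | about 4 |
| 50% | 2.15 | 3.00 | 2.54 | 83% | 75% | about 7 |
| 70% | 2.27 | 4.33 | 3.03 | 93% | 80% | about 12 |

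Losses may differ by a point from the rounded powers. The simulation error of a single power is at most √(0.25/2000) = 1.1 points. Cox recovered hazard ratios of 1.95 to 2.02.

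At N = 205 the losses are 35.4 − 35.2 = 0.2, 73.7 − 69.0 = 4.7, 91.0 − 85.0 = 6.0 and 97.2 − 88.2 = 9.0 points.

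**Step 4, if the analysis waits for the 5-year visits.** With 5 full years for everyone, the loss is about 0 to 10 points at N = 164. At N = 205 it is 41.2 − 40.8 = 0.4, 82.3 − 80.2 = 2.1, 95.0 − 92.8 = 2.2 and 98.6 − 93.6 = 5.0. This part comes from discarding event times. With 20% dropout added (N = 205), the crude odds ratios are 2.01, 2.35, 2.70 and 3.33, still below the 5-year values.

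**Step 5, no true effect.** At the year-8 cut the odds ratio centres on about 1, and type I error is 3 to 5%.

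**The case against.** Cancer outcome is not defined in item 3.2, and unlike item 3.1 it does not point to the five secondary endpoints. It could mean a binary status at a fixed time, which would suit logistic regression, with the details left to a statistical analysis plan that is not at hand. This has some force, but no such fixed-time endpoint is defined anywhere in the protocol, and the choice of model is stated there rather than deferred.

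The range of 1 to 5 years is derived, not stated. The extra year in 10.2.1 is for the primary endpoint, and every patient is scheduled for 5 years. If the analysis waits, unequal entry largely stops mattering and censoring is mainly dropout. This stands. It reduces the problem but does not remove it (step 4).

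For rare events the loss vanishes. This also stands, and may apply to local or regional failure.

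A reader might infer that logistic regression will produce false germline associations. That needs follow-up to differ materially by carrier status. In an extreme case (carriers followed 1 to 3 years, non-carriers 3 to 5), a null marker gave odds ratios of 0.51 to 0.38 across the four event rates, with false positives of 1 to 80%. A carrier share rising from 10% to 30% between accrual halves, at 35% five-year risk and a year-8 cut, gave a null odds ratio of about 0.79 but rejection of only 6.0%, against 4.6% for Cox. Nothing in the protocol suggests either pattern.

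**Conclusion.** The point holds in a limited form. For cancer outcome, item 3.2 names a model that does not fit how the protocol treats its disease outcomes in 2.2.1, 3.1 and 10.1, and it sets neither a horizon nor a censoring rule. With an analysis about 1 year after accrual ends, the odds ratio is pulled toward 1 relative to the 5-year value: barely at 10% five-year events, and from 4.33 to about 3.03 at 70%. Power falls by about 0 to 12 points under the stated assumptions on carrier share, effect size and event rates, none of which comes from the protocol. The claim is lost precision and an effect measure tied to no horizon. It is not spurious association. Response, toxicity, and the primary and secondary analyses are unaffected, and the objective is exploratory, so this is a low-priority improvement.

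**What to change.** In item 3.2, keep logistic regression for response and toxicity. For germline associations with local, regional and distant control, progression-free survival and overall survival, use the Cox model already named in item 3.1. Stratifying by cohort is optional.

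The correlative research text in section 5.4 allows germline samples at baseline, during or after treatment. Where a sample is taken after treatment, time at risk should start no earlier than the sampling date.

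If an odds ratio is preferred, define the outcome at a fixed time and state how patients censored before it are handled.

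The cost is a sentence or two of text and use of the sampling date. No new patients or visits are needed.
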